### Recruitment

2.8

Participant recruitment announcement will be posted on website of Daegu Oriental Hospital of Daegu Haany University, inside the Daegu Oriental Hospital of Daegu Haany University, and in the subway. Before the study begins, all matters relating to the study will be explained in details, ample opportunities to know about all foreseeable results will be given, and written consents will be obtained from the participants, who meet both the inclusion criteria and the exclusion criteria, and their guardians.

### Blinding

2.9

This is an open-label study comparing TEA with acupuncture treatment. It was not possible to design a double-blind for both the practitioner and the participant in this study, without revealing either the TEA or the acupuncture treatment, because of the intervention characteristics and area of application of the thread embedding treatment. In addition, the 2 groups have different number of visits.

### Statistical methods

2.10

#### Sample size

2.10.1

This clinical trial is a pilot study, and will prepare for the primary confirmation stage and basic data about prudence in the study and clinical results before the large sample size study. Hence, rather than following the separate sample counting criteria, 20 participants were selected (20% dropout rate considered) for the experimental and control groups.

#### Statistical analysis

2.10.2

This statistical analysis is based on “Clinical Trial Statistics Guide (KFDA, 2000)” and the statistical package used is IBM SPSS Win ver. 19.0. The last observation carried forward method is used for missing data from drop-outs. For statistical significance, the significance level is set at 5%, and ITT (intention-to-treat: intent-to-treat analysis) analysis and PP (per protocol) analysis are conducted for all data analyses. ITT analysis is applied in principle.

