### Study design

2.2

We will conduct a single-institution, randomized controlled pilot trial to compare the efficacy and safety of TEA with acupuncture on knee osteoarthritis.

A total of 40 participants diagnosed with knee osteoarthritis will be recruited from Daegu Oriental Hospital through advertisements. The recruitment period will run from the date of Institutional Review Board (IRB) approval to December 31, 2020. The investigator will have an interview with every potential participant by telephone and schedule screening visits. During the screening visits, every potential participant will be informed in details, ample opportunities to know about all foreseeable results will be given, and written consents will be obtained from the participants. A random assignment will be performed to divide the experimental group and the control group. The probability of being assigned to the 2 groups will be the same. The experimental group will receive TEA treatment on the knee region. The control group will receive commonly used acupoints for knee osteoarthritis treatment. The visit date will be recognized 3 days before and after the visit date and carry on for 10 weeks. A flowchart of the study is illustrated in Fig. 1, and the clinical trial schedule for treatment and outcome measurement is presented in Table 1.

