### Interventions

2.4

The participants will be randomly divided into 2 groups: the experimental group and the control group. The experimental group will receive thread embedding treatment 6 times (1 time/week) in 6 weeks on 14 defined knee areas, and the control group will receive acupuncture treatments 12 times (2 times/week) in 6 weeks on 9 defined acupuncture points.

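### Last observation carried forward is the only stated rule for drop-outs in the lead ITT analysis; it can shrink a true VAS difference, or create one if drop-out differs between arms

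*Protocol article*

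**What the plan says.** Section 2.10.2 (Statistical analysis) of the protocol article fixes the handling of drop-outs: "The last observation carried forward method is used for missing data from drop-outs". It plans both ITT and per-protocol analyses and ranks them: "ITT analysis is applied in principle". Testing is at the 5% level.

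Section 2.10.4 analyses VAS, the primary outcome, by a two-factor repeated-measures analysis of group, time and their interaction. Section 2.5 schedules VAS at baseline, week 3, week 6 and 4 weeks after treatment ends (week 10).

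Three other places bear on drop-out:

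- Section 2.10.1 (Sample size): "20 participants were selected (20% dropout rate considered) for the experimental and control groups".
- Section 2.4 (Interventions): "The experimental group will receive thread embedding treatment 6 times (1 time/week) in 6 weeks", whereas "the control group will receive acupuncture treatments 12 times (2 times/week) in 6 weeks".
- Section 2.9 (Blinding): the trial is open label and "the 2 groups have different number of visits".

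**The concern.** LOCF treats a participant's pain as frozen at the last visit attended. Entry requires VAS 4 to 7, and the objective in section 2.1 is framed around pain improvement. Someone lost before week 3 would therefore keep an entry-level score at weeks 3, 6 and 10. Someone lost after week 6 would have the end-of-treatment score carried to week 10, which would hide any return of pain. The filled-in values then enter the analysis as if they had been measured. They also flatten the time profile that the group-by-time interaction is meant to test.

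The rule is written down as the method, so this is not detail left to an analysis plan. The stake is the accuracy of the VAS difference and of its SD, which sections 2.1 and 2.10.1 intend as basic data for a larger trial.

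**Working it through.** **The protocol's own figure.** There is no power calculation to reproduce. The 20 per group fits 16 completers at 20% loss: 16 / (1 − 0.20) = 20. That loss is 0.20 × 20 = 4 participants per arm.

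**Inputs from the protocol.** 20 per arm; 1:1 allocation ("The probability of being assigned to the 2 groups will be the same", section 2.2); one overall drop-out figure of 20%; entry VAS 4 to 7; assessments at baseline and weeks 3, 6 and 10; 5% level.

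**Assumptions (the protocol gives no values).** Mean baseline VAS 5.5, the midpoint of 4 to 7. Mean fall of 1 cm by week 3 and 2 cm by week 6 in both arms. Half of drop-outs last seen at baseline and half at week 3. Drop-out unrelated to outcome within arm. Follow-up SD 1.5 to 2, correlation 0.5.

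**Formula.** With drop-out d in an arm, the expected week-6 mean under LOCF is

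(1 − d) × week-6 mean + d × (p0 × baseline mean + p1 × week-3 mean),

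where p0 and p1 are the shares of drop-outs last seen at baseline and at week 3.

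**No true difference.** Each drop-out hides 0.5 × 2 + 0.5 × 1 = 1.5 cm of improvement on average. The bias is the difference in drop-out times 1.5 cm. Rejection rates come from simulated trials of 20 per arm. They span a t test on change, ANCOVA at one time point and the planned group-by-time test.

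| Drop-out TEA / acupuncture | Losses out of 20 | Bias (cm) | Rejection at nominal 5% |
|---|---|---|---|
| 20% / 20% | 4 v 4 | 0 | near 5% |
| 15% / 25% | 3 v 5 | 0.10 × 1.5 = 0.15 | 5–6% |
| 10% / 30% | 2 v 6 | 0.20 × 1.5 = 0.30 | 7–10% |
| 5% / 35% | 1 v 7 | 0.30 × 1.5 = 0.45 | 10–18% |

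As tabulated, the bias favours TEA. Swapping the arms gives the same sizes in favour of acupuncture. At 10%/30% the planned group-by-time test alone rejected in 7.1–9.9% of trials.

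**Sensitivity to the assumptions.** If all drop-outs are lost before week 3, or all after it, the 10%/30% bias is 0.40 or 0.20 cm. Over falls of 1 to 3 cm and splits from 15%/25% to 5%/35%, it runs from 0.05 to 0.90 cm.

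**True difference of 1.0 cm** (acupuncture falls 2 cm; TEA falls 3 cm, with 1.5 cm of it by week 3). At 20% drop-out in both arms:

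- TEA: 0.8 × 2.5 + 0.2 × (0.5 × 5.5 + 0.5 × 4.0) = 2.95
- Acupuncture: 0.8 × 3.5 + 0.2 × (0.5 × 5.5 + 0.5 × 4.5) = 3.80
- Difference: 0.85 cm in place of 1.0 (0.80 to 0.90 depending on timing)

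In simulation with SD 1.5, power was 36% under LOCF and 45% on completers. With unequal drop-out the same true effect appears as 1.15 to 1.30 cm at 10%/30%, and as 0.30 to 0.65 cm at 30%/10%.

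**The case against.** The strongest reply is that the damaging scenarios are not in the protocol. Section 2.10.1 gives one drop-out figure, which is considered rather than predicted, with no split by arm. Section 2.9 cites the different visit numbers as a reason for not blinding and says nothing about attrition. At equal drop-out with no true effect, LOCF does no harm to the mean comparison or to the error rate. At 15%/25% the inflation is barely visible. All of this stands.

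A reader might infer that LOCF will favour TEA because acupuncture asks for twice as many sessions. The documents do not support a direction. TEA places 14 threads per participant in an open-label trial, so losses could equally be higher there. The claim that LOCF favours the better-retained arm also holds only while pain is still falling. If pain returns after week 6, carrying that value forward overstates lasting benefit instead.

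The trial is also a 40-person pilot without a power claim. With SD 2, the standard error of a group difference is 2 × √(2/20) = 0.63 cm, so a 0.30 cm bias is about half a standard error. That lowers the severity but does not remove the point, because the pilot's estimates are meant to feed a larger trial and the protocol still tests efficacy at 5%.

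The planned per-protocol analysis is a partial answer at best. Completers are an unbiased subset here only because drop-out was assumed unrelated to outcome; in practice a per-protocol set selects on adherence and completion.

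**Conclusion.** The point holds in conditional form. LOCF is the only stated rule for drop-outs in the lead analysis. If pain falls during treatment, it shrinks a true difference even at equal drop-out (about 1.0 to 0.85 cm at 20% per arm). If drop-out differs between arms, it can create a difference in either direction: about 0.15, 0.30 or 0.45 cm at splits of 15%/25%, 10%/30% or 5%/35%. Unequal loss is plausible given the open label and 6 versus 12 sessions, but it is not stated.

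These sizes rest on the assumed 2 cm fall, drop-out timing and SD. It would be too strong to say that LOCF necessarily biases this trial, or that its conclusions would be invalid: with equal drop-out and timing and no true effect the comparison is unbiased. What can be said is that the error cannot be predicted or allowed for in advance, and that it may distort the effect and SD handed to the next trial. This should be fixed, but it is not a bar to running the pilot.

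**What to change.** In section 2.10.2, replace the LOCF sentence. Suggested content: VAS at weeks 3, 6 and 10 will be analysed by a likelihood-based mixed model for repeated measures using all observed values, with group, week, group-by-week and baseline VAS as terms and small-sample degrees of freedom; drop-outs will be reported by arm and time; LOCF, if shown, is a sensitivity analysis only.

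Section 2.10.4 should change with it. Deleting LOCF while keeping a repeated-measures ANOVA that needs complete rows would turn the lead analysis into a completers analysis. The mixed model answers the same question about group, time and interaction. A sensitivity analysis that shifts imputed values away from missing at random is optional.

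The cost is small: a few sentences, somewhat more analysis work, and a check that the named software version supports the chosen degrees of freedom. No visit or measurement is added. The model relies on missing at random, which the data cannot verify. In this form, participants with no VAS after baseline contribute no outcome information, so their number in each arm should be reported. The change should be made before the data are analysed.

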#### Analysis of baseline characteristics

2.10.3

##### Analysis of full data

2.10.3.1

A descriptive analysis will be performed for the demographic characteristics (e.g., gender, age) and clinical characteristics of participants in baseline data. Quantitative data will be summarized using the mean with standard deviation (SD), and qualitative data will be summarized using the frequency and percentage.

##### Homogeneity test of the 2 groups (experimental and control)

2.10.3.2

Homogeneity test between groups will be performed using 2-sample *t* test or Mann–Whitney *U* test for quantitative data according to the normality, and Chi-square test will be performed for qualitative data.

#### Analysis of efficacy

2.10.4

For the primary (VAS) and secondary (SF-MPQ, WOMAC) outcomes, we will evaluate the difference of time and groups, and an interaction between the time and the groups using repeated-measure 2-factor analysis. If a significant interaction between the time and the groups was observed, we will use contrast analysis to compare individual differences between levels of the time and the groups.

For the other variables, we will evaluate the difference of the time using repeated-measure ANOVA test. When the variable measurement was implemented before and after treatment, we will calculate the change within the time, and evaluate the difference between the groups using Student *t* test as a parametric test, or Mann–Whitney test as a nonparametric test.

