#### Inclusion criteria

2.3.1

(1)50 years old and above(2)Morning stiffness to last less than 30 minutes(3)Applicable for VAS 4-7(4)Kellgren-Lawrence grade 2 to 3 on knee X-ray(5)Knee pain lasting more than 3 months(6)Consenting participants

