#### Randomization

2.3.3

Block randomization will be performed, the size of the block will be 4, then the experimental and control groups will be 2:2 for each block, the randomization codes will be assigned between the groups, and will be proceeded as a pilot study. Random numbers were generated by an independent statistician. Sealed opaque assignment envelopes were used for allocation concealment. Once the clinical trial starts, each participant, who meets the selection criteria, will be assigned to the experimental and control groups according the randomization code.

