### Outcome measurement

2.5

A series of measurements to assess VAS for pain and short form McGill pain question (SF-MPQ), Western Ontario and McMaster Universities Osteoarthritis Index (WOMAC) will be collected before clinical trial, 3 weeks after procedure, 6 weeks after procedure, and 4 weeks after the end of procedure. Outcome measurements and the following treatment schedules are summarized in Table 1.

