##### Visual analogue scale score (VAS)

2.5.1.1

VAS is a 10 cm measurement instrument to determine the severity of pain.^[16]^ A number ranging from 0 to 10 on both ends of the straight line is written down in words from no pain (0) to severe pain (10). The participant will mark on a straight line according to the degree of pain, and the investigator will measure the length to evaluate the pain.

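### The group × time analysis uses no baseline covariate and names no deciding test; if baseline is a time level, as seems intended, its group main effect estimates three quarters of the mean post-baseline effect

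*Protocol article*

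**What the plan says.** Under Outcome measurement (2.5), VAS, SF-MPQ and WOMAC "will be collected before clinical trial, 3 weeks after procedure, 6 weeks after procedure, and 4 weeks after the end of procedure". That makes one pre-treatment and three post-baseline values, at about weeks 3, 6 and 10.

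Under Analysis of efficacy (2.10.4), for all three outcomes, "we will evaluate the difference of time and groups, and an interaction between the time and the groups using repeated-measure 2-factor analysis". The next step is conditional: "If a significant interaction between the time and the groups was observed, we will use contrast analysis to compare individual differences" between levels of time and group. No covariate is named. Change scores compared by a t test or Mann–Whitney test are described only after the text has turned to other variables. Baseline comparability is handled by homogeneity tests (2.10.3.2), which do not enter the efficacy model.

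VAS is a 0 to 10 cm scale (2.5.1.1) with no primary time point attached. Entry requires "Applicable for VAS 4-7" (2.3.1). The significance level is 5% (2.10.2). On size, "20 participants were selected (20% dropout rate considered) for the experimental and control groups" (2.10.1), expressly without a formal calculation.

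**The concern.** Randomisation makes the expected group difference at baseline zero. If the baseline value is one of four equally weighted levels of time, the group main effect averages that zero with the three post-treatment differences, so it does not estimate the treatment effect on any post-treatment scale. The group difference is one of the three tests that the plan lists. If the interaction is not significant, no contrasts follow, and the main effect is the only comparison of the groups left.

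This matters because the pilot is meant to supply basic data for a larger trial (2.1, 2.10.1). A planner who took the main effect as the effect size, with the SD held fixed, would inflate the next sample size by 1/0.75² = 1.78.

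If baseline is instead left out of the time factor, the dilution disappears, but a prognostic value that the trial already collects is not used.

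**Working it through.** **Inputs from the protocol.** Four measurement times, one before treatment; 20 per group, 1:1; 5% level (taken as two-sided); no covariate. The protocol gives no effect size, SD, correlation or power, so there is no power figure to reproduce. Its 20 per group is consistent with 16 completers per group: 16/(1 − 0.20) = 20.

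**Step 1: what the main effect estimates.** In a balanced 2 × 4 layout, with post-baseline effects d₁, d₂, d₃:

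E(group main effect) = (0 + d₁ + d₂ + d₃)/4 = 0.75 × (d₁ + d₂ + d₃)/3.

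The factor 0.75 holds for any effect profile when measured against the mean post-baseline effect. For a constant 1.0 cm it gives (0 + 1 + 1 + 1)/4 = 0.75 cm. Against the week-6 effect the ratio depends on the profile:

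| Effect at baseline, weeks 3, 6, 10 | Main effect ÷ week-6 effect |
|---|---|
| 0, 1, 1, 1 | 0.75 |
| 0, 0.5, 1, 1 | 0.625 |
| 0, 0.5, 1, 0.5 | 0.50 |

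**Step 2: what the interaction does.** Its null concerns only differences between times, with baseline as one of them. It is therefore not diluted, and it subtracts baseline differences. With four levels and two groups it has (4 − 1)(2 − 1) = 3 degrees of freedom and yields no single effect estimate.

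**Step 3: illustrative power.** Assumptions, none from the protocol: baseline VAS uniform over the entry range, so SD = 3/√12 = 0.87; follow-up SD 2; correlation 0.4 with baseline and 0.6 between follow-ups; constant effect 1.0 cm; 20 per arm.

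- Main effect: variance of the four-time mean = [0.75 + 3(4) + 6(0.4)(0.866)(2) + 6(0.6)(4)]/16 = 31.31/16 = 1.957. SE = √(1.957 × 2/20) = 0.442. Noncentrality = 0.75/0.442 = 1.70, df 38, power 38%.
- Mean of three follow-ups, unadjusted: variance = [12 + 14.4]/9 = 2.933. SE = 0.542. Noncentrality = 1.85, power 44%.
- The same mean, adjusted for baseline: covariance with baseline = 0.4 × 0.866 × 2 = 0.693. Residual variance = 2.933 − 0.693²/0.75 = 2.293. SE = 0.479. Noncentrality = 2.09, df 37, power 53%, or 52% after allowing for the estimated covariate slope.
- Interaction (3-df multivariate test): noncentrality 4.35, df 3 and 36, power 35%.

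Simulations under these assumptions (baseline drawn as uniform or as normal with the same SD, interaction tested in more than one form) gave 36–38% for the main effect, 34–39% for the interaction and 51–52% for ANCOVA. For 1.5 cm they gave 69–70%, 70–75% and 85–86%. For 1.0 cm with 16 per arm the main effect had 32–33% and ANCOVA 43–44%.

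**Step 4: other assumptions.** Constant effect of 0.8 SD, equal SDs, one common correlation, 20 per arm:

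| Correlation | Main effect | Interaction | Baseline-adjusted mean |
|---|---|---|---|
| 0.3 | 77% | 56% | 96% |
| 0.5 | 65% | 73% | 97% |
| 0.7 | 56% | 93% | 99% |

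Which planned test does better depends on the correlations. The baseline-adjusted comparison beats both in every row.

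**The case against.** The strongest objection is that the same sentence plans a group-by-time interaction and the next one builds contrasts on it. With baseline as a time level, that interaction carries the treatment effect, and the protocol does not make the main effect decisive. This stands. A reader might infer that the plan's treatment test as a whole is diluted to three quarters, or that it leaves chance baseline imbalance uncorrected. The document supports neither: the dilution belongs to one of three listed tests, and the interaction and any contrast against baseline compare change between groups. What the objection does not supply is an effect estimate when the interaction is not significant, or a statement of which test decides.

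A contrast of mean follow-up minus baseline is available within the same model and, under the Step 3 assumptions, has about the power of ANCOVA (53% against 52% by simulation). This also stands, but the plan reaches contrasts only through a significant interaction.

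Baseline as a time level is inferred, since the protocol does not say so. This is conceded; the absence of a baseline covariate holds on either reading.

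Finally, this is a pilot with no power calculation, and an article may leave model detail to a fuller document. It would be wrong to read the power figures as showing that 20 per group is inadequate or miscalculated. The article does, however, state the model for its primary outcome, a 5% level and the aim of comparing pain improvement, so the form of that model can fairly be reviewed.

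**Conclusion.** The point holds in limited form. The protocol analyses its three efficacy outcomes without a baseline covariate and does not name the deciding test. If baseline is a level of time, the group main effect estimates exactly 0.75 of the mean post-baseline effect; that factor needs no assumption about variances or effect profile. The interaction is sound but unspecific. Under the assumed values both planned tests have roughly 13 to 18 percentage points less power than a baseline-adjusted comparison at 1.0 cm and 20 per arm. The size of that gap rests on SDs and correlations that the protocol does not give. The narrow entry range for VAS does not by itself establish a fault in the variance assumptions, and none is claimed. The recommendation is a free improvement in efficiency and clarity; it does not correct an invalid analysis.

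**What to change.** Take the baseline value out of the outcome vector. Compare groups over weeks 3, 6 and 10 with the outcome's own baseline as covariate, either by ANCOVA on the mean of the three follow-ups or by a mixed model with group, week, group-by-week and baseline. State in advance which group contrast decides the comparison, and report it with its confidence interval whether or not the interaction is significant. Do the same for SF-MPQ and WOMAC.

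The cost is a change of analysis wording and one degree of freedom. Baseline is already collected, so no visit, measurement or participant is added.

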### Objective

2.1

The aims of this pilot trial are to compare pain improvement between the TEA and the acupuncture groups with knee osteoarthritis, to establish the feasibility of future TEA research, and to provide clinical evidence of the basic data before the large sample size study.

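### Visit-specific TEA-versus-acupuncture contrasts on VAS are run only after a significant group-by-time interaction, so the pilot's planning estimate is either not produced or selected on significance

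*Protocol article*

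**What the plan says.** Section 2.10.4 puts VAS, SF-MPQ and WOMAC through the same model: "we will evaluate the difference of time and groups, and an interaction between the time and the groups using repeated-measure 2-factor analysis". Comparisons between levels of time and group come next, under a condition: "If a significant interaction between the time and the groups was observed, we will use contrast analysis to compare individual differences". The second paragraph of that section offers a change-score comparison by t test or Mann-Whitney test. It is introduced for variables other than these three, so it does not clearly cover VAS.

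Section 2.5 lists four assessments, which "will be collected before clinical trial, 3 weeks after procedure, 6 weeks after procedure, and 4 weeks after the end of procedure". Section 2.5.1.1 defines VAS as a 10 cm scale without naming a time point or summary measure. Section 2.10.2 sets the significance level at 5%.

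Section 2.1 says the pilot is to compare pain improvement between the groups and "to provide clinical evidence of the basic data before the large sample size study". Section 2.10.1 sets the size without a power calculation ("rather than following the separate sample counting criteria"): "20 participants were selected (20% dropout rate considered) for the experimental and control groups".

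**The concern.** The natural planning quantity from this pilot is the difference in VAS between TEA and acupuncture at a defined visit, with its uncertainty. Under section 2.10.4 that contrast is computed only when the interaction test reaches 5%, in a trial that was not sized for any test.

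This has two effects. When the interaction is not significant, the plan leaves only the group main effect, which is diluted by the pre-treatment visit and is not the effect at any visit. When it is significant, the contrast comes from the trials in which chance enlarged the difference, so it overstates the truth on average. A larger trial planned on either figure would start from a poor estimate.

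**Working it through.** **Inputs from the article.** 20 per arm with 20% dropout considered, which corresponds to 20 × (1 − 0.20) = 16 completers per arm (a number the article does not state); equal allocation; four assessments; 5% level; baseline VAS between 4 and 7 (section 2.3.1). Last observation carried forward would keep the intention-to-treat analysis at up to 20 per arm, so 16 and 20 bracket the case.

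**Inputs assumed.** The article gives no SD, correlation or effect size. Baseline SD is taken as 0.9 cm (close to uniform on 4-7), follow-up SD as 2.0 cm (range 1.5-2.5) and correlation as 0.5 (range 0.3-0.7). The true difference is half-size at week 3 and full size at week 6 and at the 4-week follow-up.

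**Step 1: the unconditional quantity.** The group main effect averages the visit differences. With true differences of 0, 0.5, 1.0 and 1.0 cm:

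(0 + 0.5 + 1.0 + 1.0) / 4 = 0.625 cm.

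Simulation returns 0.62-0.63 cm. The main effect therefore understates the 1.0 cm difference by more than a third.

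**Step 2: the conditional quantity.** The planned 2 × 4 repeated-measures analysis was simulated 8,000 times per scenario. The interaction F test used the Greenhouse-Geisser correction at 5%. The week-6 difference in change from baseline was averaged over the trials with a significant interaction. At SD 2.0 and correlation 0.5 (the lower run rate and the higher inflation belong to 16 per arm):

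| True week-6 difference | Contrasts run (16 to 20 per arm) | Mean estimate when run ÷ truth |
|---|---|---|
| 0 cm | 5% | n/a |
| 0.5 cm | 9-10% | about 2.0 |
| 1.0 cm | 25-31% | 1.4-1.5 |
| 1.5 cm | 56-69% | 1.14-1.20 |
| 2.0 cm | 84-93% | 1.03-1.06 |

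Averaged over all trials, without the condition, the week-6 difference equals the true value. The inflation comes from the selection alone. Simulation error on the percentages is about half a percentage point.

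**Step 3: sensitivity to the assumptions.** Over the full assumed range of SD, correlation and arm size:

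| True week-6 difference | Contrasts run | Mean estimate when run ÷ truth |
|---|---|---|
| 0.5 cm | 6-23% | 1.6-2.5 |
| 1.0 cm | 12-77% | 1.1-1.7 |
| 1.5 cm | 26-99% | 1.0-1.4 |
| 2.0 cm | 48-100% | 1.0-1.2 |

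A different correlation pattern (0.6 between follow-ups, 0.4 with baseline, SD 2.0, 20 per arm, true 1.0 cm) gives 36% and a mean of 1.46 cm, which agrees.

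**Step 4: what an unconditional contrast delivers.** The 95% CI half-width for an unadjusted week-6 comparison is t × SD × √(2/n):

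- 20 per arm: 2.024 × 2.0 × √(2/20) = 1.28 cm (0.96 to 1.60 cm over SD 1.5-2.5)
- 16 per arm: 2.042 × 2.0 × √(2/16) = 1.44 cm (1.08 to 1.81 cm)

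The interval is wide, but it is available in every trial and its centre is not selected on significance.

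**The case against.** An omnibus test followed by contrasts is a conventional guard against testing every visit, and this is a declared pilot with no powered hypothesis. The condition governs contrast tests. Nothing in the article withholds VAS means and SDs by arm and visit, and a planner could work from those. The group effect is evaluated regardless. Table 1 is not shown, and a full protocol or analysis plan may name a primary time point.

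Much of this stands. It limits the point to visit-specific contrasts, makes the missing time point the weaker half, and lowers the severity. It does not remove the condition, which is a stated rule. Guarding against several visit tests is also better done by naming one visit in advance.

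A reader might infer more than the article supports:

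- **That the pilot usually gives no treatment-effect estimate.** The main effect is always assessed. How often the contrasts are run depends on a true difference the article does not give; at 1.5-2.0 cm they are run in most trials under the central assumptions.
- **That the false-positive rate is about doubled**, because either the main effect or the interaction could be called a positive result. The article states no such decision rule.
- **That a constant benefit at all follow-ups would never open the contrasts.** This would need baseline left out of the model, but section 2.5 lists baseline among the measurements. With it included, a constant 1.0 cm benefit gives a significant interaction in roughly 35-39% of simulated trials (20 per arm, SD 2.0).
- **That the larger trial would be undersized by a known amount.** The article does not say that trial would be planned on the conditional contrast alone.

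**Conclusion.** The point holds in a limited form. Section 2.10.4 makes visit-specific VAS contrasts conditional on a significant interaction, and the text shown fixes no primary time point. What remains unconditional is a main effect diluted by baseline. This conflicts with the aim of supplying basic data for a larger trial.

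The size depends on assumptions about SD, correlation and true effect that are not in the article. With SD about 2 cm and correlation about 0.5, the problem is marked for true differences up to about 1 cm: the contrasts are mostly not run, and are inflated 1.4 to 2 times when they are. It is minor at 2 cm. The direction of the bias, upward when selected on significance, does not depend on those values. Severity: should be fixed.

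**What to change.** In section 2.10.4:

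1. Delete the significant-interaction condition for VAS.
2. Name one between-group VAS contrast at a single time point as primary. Week 6, the end of treatment, is one candidate; if the full protocol already names a time point, use that.
3. Report that contrast, preferably adjusted for baseline VAS, with its 95% CI whatever the interaction test shows.
4. Label the other visits, the group main effect and the interaction as secondary.

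The cost is two sentences and no new data, visits or participants. The sponsor gives up one thing: a significant interaction or main effect alone would no longer count as the primary result.
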